### 1.2 Objectives and hypotheses

The purpose of this study is to determine the optimal intensity of RBT post-stroke. The 'optimal' intensity is the intensity that improves reactive balance control in fewer sessions, without any apparent negative consequences (i.e., no increase in adverse outcomes). We expect that high-intensity training (50% above the multi-step threshold) will improve reactive stepping ability faster than moderate-intensity training (at the multi-step threshold). If the first reactive step is not effective in avoiding a fall after a loss of balance, additional steps must be taken; therefore, the number of steps needed to recover from a loss of balance is a global indicator of the effectiveness of balance reactions. We will assess reactions to novel, untrained, balance perturbations throughout training, and calculate the rate of decline in average number of steps taken to recover balance (i.e., learning rate). Retention of learning will be assessed one week post-training. Our primary hypotheses are:

- 1) Adaptation rate will be faster for high-intensity RBT than moderate-intensity RBT;
- 2) Adaptation rate will be faster for both RBT groups than a walking control group; and
- 3) Both RBT groups will have better retention of learning than the walking control group; i.e., the RBT groups will take fewer steps to respond to the novel perturbation than the walking control group one week post-training.

Secondary objectives are to compare the rate of adverse outcomes between groups, and to determine the effect of different intensities of RBT on the mechanisms underlying improved reactive stepping ability, functional balance, falls efficacy, and participation in daily activities.

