## 2.6 Sample size justification

Our primary outcome is learning rate. The sample size for each group was estimated as  $\lambda/\Delta$ , where  $\lambda$  was obtained from tables for 3 groups using probability of a Type 1 error ( $\alpha$ ) of 0.05, probability of a Type II error ( $\beta$ ) of 0.2; therefore,  $\lambda$  of 9.64 was used. Additionally:

$$\Delta = \frac{1}{\sigma^2} \sum_{i=1}^k (\mu_i - \bar{\mu})^2$$

where  $\sigma$  is the standard deviation,  $k$  is the number of groups (3),  $\mu_i$  is the mean for each groups and  $\bar{\mu}$  is the mean for all groups combined. From pilot data, we estimate a standard deviation of 9.7 for the learning rate. People with stroke typically require 3-4 steps to regain stability following the perturbation magnitudes used in the proposed study. Due to the mechanical challenges of the perturbation, at minimum 1 step is required to respond to the perturbation (i.e., young healthy adults would take 1 step to respond to the perturbation). Therefore, an improvement from 3-4 steps pre-training to 1-2 steps post-training is considered clinically meaningful, and a much larger effect size would likely not be possible. From previous studies an improvement from taking, on average, 3-4 steps pre-training to 1-2 steps post-training is feasible. Simulating learning rates between these data points (Figure 5), we expect that learning rates of approximately 0.4 ( $\mu_1$ ), 2 ( $\mu_2$ ) and 10 ( $\mu_3$ ) for the high-intensity, moderate-intensity, and walking control groups, respectively, would show meaningful differences between the three groups. Therefore,  $\Delta$  was calculated as 0.56, giving a target sample size of 17 per group or 51 participants total. To account for a ~20% rate of withdrawal, we will aim to recruit 21 participants per group, or 63 participants total. Enrolment will stop when 51 participants have completed the retention test, or 63 participants have been enrolled, whichever happens first.

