## 2.7 Analyses

One-way analysis of covariance (ANCOVA), with sex as a covariate, will be used to compare learning rates between the 3 groups. ANCOVA, controlling for the pre-training value, will be used to compare the following outcomes between the 3 groups at the post-training and retention time points: average number of steps, step initiation time, step execution time, step length, braking impulse, margin of stability, mini-BEST, and FES-I. Pre-planned contrasts will be used to compare outcomes between the high- and moderate-intensity groups, and between the two RBT groups combined and the walking control group. Alpha will be 0.05 for the primary outcome (learning rates), and adjusted for multiple comparisons using the Holm-Bonferroni method for secondary outcomes. Falls and quality of life data will be reported without inference so that these data can be used in meta-analyses and/or as pilot data for future studies.

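### Hypotheses 2 and 3 claim that both RBT groups beat walking, but the only planned contrast with walking pools them, so a significant result does not show that each intensity works

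*Protocol*

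**What the plan says.** Section 1.2 of the protocol gives three primary hypotheses. The second reads "Adaptation rate will be faster for both RBT groups than a walking control group". The third begins "Both RBT groups will have better retention of learning than the walking control group" and is then spelled out as fewer steps in response to the novel perturbation one week after training.

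Section 2.7 gives the analysis: "One-way analysis of covariance (ANCOVA), with sex as a covariate, will be used to compare learning rates between the 3 groups". Average number of steps at retention is compared by ANCOVA adjusted for the pre-training value. Two contrasts are pre-planned for these outcomes: high against moderate intensity, and a comparison "between the two RBT groups combined and the walking control group". No contrast sets a single RBT group against walking. Alpha is 0.05 for learning rates, and secondary outcomes are adjusted by Holm-Bonferroni.

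Section 2.6 sizes the trial for the three-group comparison of learning rates, at 17 completers per group.

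**The concern.** Read as written, hypotheses 2 and 3 are joint statements: high intensity beats walking, and moderate intensity beats walking. The pooled contrast tests something weaker, namely that the mean of the two RBT groups differs from walking. One effective arm can carry it. High against moderate does not fill the gap, because it involves no control group. The three-group ANCOVA does not fill it either, because it rejects for any difference among the groups.

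This matters for how the results would be used. Section 4.1 looks ahead to clients who cannot tolerate high-intensity perturbations and suggests that they would need a longer duration of RBT. That inference needs evidence that the lower intensity itself beats walking, and no planned contrast supplies it. Section 1.1 raises the possibility that people with stroke would not tolerate high intensity, so benefit in one arm only is a realistic case.

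**Working it through.** **Inputs (section 2.6).** Expected learning rates x are 0.4 (high), 2 (moderate) and 10 (walking); a smaller x means faster adaptation. On spread, the protocol says "we estimate a standard deviation of 9.7 for the learning rate". λ is 9.64, with α 0.05 and β 0.2. The target is 17 per group.

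**Assumptions added here.** Contrasts are two-sided at 0.05 (the protocol does not state sidedness), with rejections counted in the favourable direction. The SD is common to all groups. A non-working arm has the walking mean of 10. Degrees of freedom are 51 − 3 − 1 = 47 (three groups and the sex covariate).

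**The protocol's own figure.**
- Grand mean = (0.4 + 2 + 10)/3 = 4.133.
- Δ = [(0.4 − 4.133)² + (2 − 4.133)² + (10 − 4.133)²]/9.7² = 52.91/94.09 = 0.562.
- n = 9.64/0.562 = 17.1, so 17 per group reproduces.

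**Pooled contrast.** SE = 9.7 × √(1/17 + 1/34) = 2.88. Power is from the noncentral t.

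| True means (high, moderate, walking) | Walking minus RBT average | Difference/SE | Pooled contrast significant |
|---|---|---|---|
| 0.4, 2, 10 (planned) | 10 − 1.2 = 8.8 | 3.05 | 85% |
| 0.4, 10, 10 (only high works) | 10 − 5.2 = 4.8 | 1.67 | 37% |
| 10, 2, 10 (only moderate works) | 10 − 6 = 4.0 | 1.39 | 27% |

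With 21 per group, the full recruitment target with no withdrawals, the last two rows become 44% and 33%. Enrolment stops once 51 participants complete the retention test, so 17 per group is the relevant case.

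**What the other planned contrast adds.** If only high works, high against moderate is significant in 81% of trials. Both planned contrasts are significant together in about 30% of all trials, and the pooled one alone in about 7% (simulation, 200,000 runs). The 30% pattern matches hypotheses 1 and 2 together, although moderate has no effect in this scenario.

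**Separate contrasts with walking.** SE = 9.7 × √(2/17) = 3.33.
- High against walking, planned means: 9.6/3.33 = 2.89, power 81%.
- Moderate against walking, planned means: 8/3.33 = 2.40, power 65%.
- Both significant, planned means: 59% by simulation (70% at 21 per group).
- Both significant when only one arm works: about 2.5%.

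Under the planned means, the pooled contrast is significant while at least one of the separate contrasts is not in about 26% of trials.

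**The case against.** The strongest reply is that the two contrasts are a conventional orthogonal pair that uses the two degrees of freedom of three groups, and that the stated purpose, finding the optimal intensity, is served mainly by high against moderate. If only high works, that contrast is significant in 81% of trials, so a misleading pooled result would usually come with a visible gap between the RBT arms. This stands as a limit on the harm. It does not close the gap, since a difference between the RBT arms does not say whether the weaker one beats walking.

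It can also be said that 'both RBT groups' may loosely mean RBT as a whole, and that an SAP not at hand could add contrasts. The loose reading is possible, and rewording would then settle the matter. But the protocol does not leave the contrasts open: it names them as pre-planned, and they do not match its primary hypotheses as worded.

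Two stronger readings are tempting. A reader might infer that the trial will report a false 'both' in 37% of cases. The protocol states no rule that turns a significant pooled contrast into that claim, and 37% belongs to one extreme scenario: moderate exactly null and high at its full planned effect. A reader might also want a matching percentage for retention. The protocol gives no SD or effect size for step count, and section 2.7 puts secondary outcomes under Holm-Bonferroni without stating the family size, so no such figure can be supported.

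**Conclusion.** The mismatch is real. No planned test addresses either RBT group alone against walking, so hypotheses 2 and 3 cannot be confirmed as worded. For learning rate, the pooled contrast is significant in about 37% of trials if only high intensity works and about 27% if only moderate works; requiring both separate contrasts brings a false 'both' down to about 2.5%. These figures rest on the planning values and on the assumptions listed with the working. For retention the point is one of logic only and carries no number. It should be fixed before analysis. It is not fatal, because rewording the hypotheses would also reconcile the text without changing design, data or sample size.

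**What to change.** In section 2.7, add pre-planned contrasts of high against walking and moderate against walking, and state that 'both' will be claimed only if each is significant.

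- **Learning rate (hypothesis 2):** test each at two-sided 0.05. No further correction is needed for the joint claim, because it fails whenever either component fails. That argument does not cover a claim about one arm alone, made from whichever contrast succeeds.
- **Steps at retention (hypothesis 3):** test each at the level left by the Holm-Bonferroni procedure, unless the protocol states that retention is a primary outcome outside the Holm family.

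The pooled contrast may stay, for a claim about RBT on average. Alternatively, keep section 2.7 as it is and reword hypotheses 2 and 3 to RBT on average.

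The text change is short and needs no new data. The cost of the first option is power: on the planning values, 59% for 'both' on learning rate, against 85% for the pooled contrast and the 80% target in section 2.6. Section 2.6 should say so. Restoring 80% for 'both' would take about 26 completers per group, or 3 × 26 = 78 in all; the fix does not require this.

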### 3.2 Risk management

#### 3.2.1 Balance testing and training

With appropriate screening, the risks of study procedures and interventions are minimal. RBT can be completed by people with stroke with few adverse events. Mild adverse events related to RBT included delayed-onset muscle soreness, fatigue, or exacerbation of joint pain (11%, 7%, and 32% of participants, respectively), which did not require medical attention, but resulted in modifying the intervention until they resolved (typically by the following session). Of note, the frequency and severity of adverse events were similar for the RBT group and control group, who completed more ‘traditional’ balance training. When more frequent or severe adverse outcomes are reported in RBT, this is typically due to use of very high intensity perturbations (where participants fall into the safety harness) or increased reports of anxiety related to the perturbations. We will avoid using these very high intensity perturbations to reduce the risk of more severe adverse outcomes. Participants will wear a safety harness attached securely overhead to prevent falling during training, and training sessions will be overseen by a licenced physiotherapist with experience conducting RBT. Additional actions may be taken to prevent risk of injury for specific participants (e.g., wearing an ankle brace for participants with ankle instability).

As the assessment and intervention includes tasks that are challenging to balance control, there is a small risk that participants will lose their balance and fall. Appropriate precautions will be taken to ensure patient safety during these tasks. Interventions will be administered by a trained and licensed physiotherapist. Assessments will be completed by a trained research assistant with a health sciences background. A safety harness attached to a secure point overhead will be worn for all postural perturbations to prevent a fall to the floor if the individual fails to regain stability. We have administered tens of thousands of postural perturbations to over 500 people with varying balance abilities in previous research studies and clinical activities and no participant suffered an injury as a result of an induced postural perturbation. However, even if the participant is caught by the safety harness, there is a very small chance that participants will suffer a physical injury (e.g., sprain or bruise). In the event of a minor physical injury, the physiotherapist will provide first aid, will advise the participant regarding follow-up with a medical professional (e.g., family doctor) and home treatment (e.g., rest, ice, compression, elevation), and will follow-up with the participant after a day or two.

### 3.2.2 Health status

Participants will be withdrawn if their health changes such that they would no longer be eligible for the study (i.e., one of the exclusion criteria applies to them). Changes in health status may be communicated to the research team via Epic or directly from the participant.

### 3.2.3 Privacy and confidentiality

Personal information is any information that could identify participants. If participants agree to join this study, the following personal information will only be accessible to the research team, for contact purposes:

- name
- telephone number and/or e-mail addressed (based on participant preference)
- address
- telephone number of alternative contact

A number of steps will be taken to ensure protection of personal health information. All information collected during this study, including the participant's personal information, will be kept confidential and will not be shared with anyone outside the study unless required by law. Electronic data will be stored on secure UHN servers for 10 years. After 10 years the data will be deleted from the UHN servers. Electronic files containing patient names and contact information will be password protected, and will be stored separately from study data. Hard copies of files containing de-identified data will be stored in locked cabinets and/or in offices that are locked when not occupied. Consent forms will be stored in locked cabinets/offices separately from other data. Only those individuals who require access to the data for the purpose of this study will be provided with the password to the file containing identifiers and/or the keys to the locked cabinet/office.

Video recordings of participants during the balance tests will remain within the study team, unless an optional media consent form was completed by the participant (Appendix G); in which, members of the research team could show the images only to limited academic audiences (e.g., at scientific/clinical conferences or in lectures to university students). Presenting data, including images from the study, to other researchers and students helps to share our study findings with people who can use the findings of the study. Alternatively, the images could be shown to the general public, including being posted on public websites, like YouTube. Sharing information about our study publicly helps more people to learn about our study findings. In this case, the images may be easily copied, downloaded and reused by people outside of the research team.

## 3.3 Follow-up with participants

Participants will be asked to complete a Research Volunteer Satisfaction survey (Appendices H & I) when they complete the study. The purpose of the survey is for us to learn more about the experiences of the research participants in this study. This information may be used in the design of future studies. Participants may choose to complete the survey anonymously, but may also wish to provide their contact information for follow-up with the principal investigator. Completed surveys will be stored separately from participants' study file. Participants will receive a letter of appreciation at the end of the study (Appendix J).

## 4. IMPACT

### 4.1 Significance

A high rate of falling is a common after stroke, and fall risk is highest in the first months post-discharge from rehabilitation. RBT is a novel type of exercise that aims to improve reactive balance control,

rather than ‘traditional’ balance training, which focuses on maintaining stability during voluntary movement. Time in stroke rehabilitation is limited, and physiotherapists report lack of time is a barrier to implementing RBT. The results of the proposed study will inform clinicians about the optimal RBT training parameters to improve reactive balance control and reduce risk of falling post-stroke. We expect to find the high intensity RBT leads to faster improvements in reactive stepping ability than moderate intensity RBT. This finding would suggest that clients can achieve the same benefits from a short duration of high-intensity RBT as for a longer duration of moderate-intensity training. Therefore, clinicians with limited time in rehabilitation can use high-intensity RBT to improve their clients’ reactive balance control in a short amount of time, without sacrificing time spent on other important rehabilitation goals. Alternatively, if a client is unable to tolerate high-intensity perturbations, then the study findings would suggest that a longer duration of RBT would be needed to improve reactive balance control.

## 4.2 Knowledge translation

Study results will be shared with the academic community via publication in peer-reviewed journals and presentations at conferences. We will share results directly with physiotherapists through interactive workshops (e.g., at the Canadian Physiotherapy Association meeting). The results of the trial will be incorporated into our RBT toolkit.

## 5. LIST OF APPENDICES

| Appendix | Description                                | Version date  |
|----------|--------------------------------------------|---------------|
| A        | Advertisement poster                       | 15 July 2024  |
| B        | Study brochure                             | 18 April 2024 |
| C        | Consent form                               | 29 July 2024  |
| D        | Eligibility checklist                      | 12 April 2024 |
| E        | Falls reporting questionnaire              | 18 April 2024 |
| F        | Chart review form                          | 8 May 2024    |
| G        | Optional media consent form                | 18 April 2024 |
| H        | Volunteer satisfaction survey              | 18 April 2024 |
| I        | Volunteer Satisfaction survey cover letter | 8 May 2024    |
| J        | Letter of appreciation                     | 4 July 2024   |
| K        | Falls reporting calendar                   | 4 July 2024   |
| L        | Initial contact template (Epic)            | 4 July 2024   |

